### Other secondary objectives

Other secondary objectives are to determine the influence of gender on the patients’ reactions, the anesthesia safety variables including hemodynamic stability, the frequency and quantity of postoperative nausea, vomiting and pain, the discharge times, the pharmacoeconomics and the recovery on the first postoperative day (1^st^ POD).

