Maintenance: All patients will receive a postoperative nausea and vomiting (PONV) prophylaxis with 8 mg dexamethasone and 4 mg ondansetron, if the Apfel-Score is ≥2. Analgesia will be maintained with remifentanil injection via infusion pump at a rate of 0.15 μg kg^−1^ min^−1^. Dosage will be adapted according to clinical needs based on the patient’s hemodynamic (difference of NIBP and HR greater than 20 % from baseline), autonomic (sweating, salivation, or flushing) and somatic (movement or swallowing) signs. Twenty minutes before the estimated end of surgery, all patients will receive 0.05 to 0.1 mg kg^−1^ piritramide and 15 mg kg^−1^ metamizole i.v. The inspired oxygen concentration will be adjusted to 35 to 50 %, or above this range if medically indicated. The end-expiratory CO_2_ level during the maintenance of anesthesia should be kept between 36 and 45 mmHg. The use of muscle relaxants is undesired, except for emergency situations. Spontaneous breathing or controlled ventilation with LMA will be applied during maintenance of anesthesia, according to the standard operating procedure of each participating center. Inspired desflurane concentrations of >8 vol. % and sevoflurane >2.2 vol. % have to be avoided. The systolic blood pressure should be kept at ≥90 mmHg (or ≥65 mmHg for mean arterial blood pressure), and a relative variation > 20 % from baseline values has to be avoided and requires appropriate treatment. If indicated additional bolus injection of propofol is permissible in patients.

End of anesthesia: At five minutes before planned termination of surgery, remifentanil will be discontinued. The LMA will be removed when the upper airway reflexes are fully recovered and the respiratory function is adequate (regular spontaneous breathing with a frequency of at least eight breaths per minute and SaO_2_ >95 %) and when the patient opens his/her eyes on request or is able to follow any other requests. In addition, the patient has to be hemodynamically stable before removal of LMA. The patients will be admitted to the Post Anesthesia Care Unit (PACU) following surgery. They will receive 0.05 mg kg^−1^ piritramide if the visual analog scale (VAS) for pain is more than 30.

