### Participant timeline

A participant chart is shown in Additional file 1. Eligible patients, scheduled for surgery, will be presented to the anesthesia department for the general anesthesia consent preoperatively. Additionally, a blinded sub-investigator will explain the nature and purpose of the study to these patients and seek a written informed consent for the study (time point A, before surgery). The same investigator will collect the following baseline characteristics after the patient enrollment (time point A):AgeSexWeightHeightBMISmoking status (nonsmoker, current smoker-amount of pack years, ex-smoker)Contraceptives (woman - yes/no)Pre-existing diseases and medical/surgical historyClassification according to the American Society of Anesthesiologists (ASA)Apfel ScoreBaseline (Postoperative Quality Recovery Scale) PQRS testing prior to surgery (see Additional file 2)

Shortly before surgery on the same day (time point B), an unblinded investigator will randomize the patients with sequentially numbered, opaque, sealed envelopes (SNOSE).

The same unblinded investigator will perform anesthesia (time point C, surgery) and assess the intraoperative variables in the respective patient:Depth of anesthesia (BIS)Standard safety parameters: ECG, SpO_2_ and end-tidal CO_2_, and NIBPVentilation pressure parameters: Ppeak, Pmean, and PEEPType of performed surgeryRecording of the end-expiratory applied volatile anesthetic concentration/applied amount of propofol for maintenancePharmacoeconomics: Total amount of intraoperative required catecholamines, of additionally applied propofol as rescue medication, of wasted propofol at the end of the surgery in the propofol group and of intraoperative remifentanil and piritramide consumption.Time points of anesthesia induction, LMA insertion, administration of the study treatments, anesthesia and surgery durationFrequency of intraoperative (induction/maintenance) coughs and laryngospasms

The blinded investigator will enter the operating room at the time point T_0_, which starts with cessation of anesthesia and application of maximum fresh gas flow and predefines the measurement start-time point for the time variables. The unblinded investigator will ensure that the blinded individual is precluded from recognizing which anesthetic was used, by masking the ventilator. The blinded investigator will assess the following postoperative variables during time point D:

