Assessment of airway reactionsFrequency of CE and LSEEmergence times: TSB, TLR, TOE, TRC, TSNThe modified Aldrete scores with a 10-point scale will be recorded 5 minutes after removal of LMA (see Additional file 3)

Time point E starts with admission of the patient to the PACU. The blinded investigator will assess the following variables:The modified Aldrete scores with a 10-point scale will be recorded every 15 minutes until discharge from the PACU (see Additional file 3)Time-point of readiness to be discharged from the PACU (Aldrete Score ≥9) (see Additional file 3)Assessment PQRS-T40, which is 40 minutes after the time point T_0_ (see Additional file 2).The VAS pain score will be self-evaluated and recorded by 100-mm visual analog scale (VAS) (with 0 corresponding to no pain and 100 corresponding to maximal pain) every 15 minutes after admission to the PACU. For postoperative analgesia, the patients will receive 0.05 mg kg^−1^ piritramide, in order to maintain a VAS pain score ≤30 mm

Other measurements in the PACU (blinded assessor) include the following:Nausea in the PACU will be evaluated using an 11-point verbal rating scale (VRS) (with 0 corresponding to no nausea and 10 corresponding to extreme nausea) at admission and discharge from the PACU and every 15 minutes in the PACUCount of vomiting in the PACUConsumption of piritramide in the PACU

Time point E: First post-op day: (telephone interview/ visit at ward):PQRS-D1 (see Additional file 2)

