### Statistical methods

All efficacy, safety and economical results will be presented on the Intention to Treat (ITT) data set, which will be composed of all randomized patients. In case it appears necessary, we will define a secondary Per Protocol (PP) data set prior to the database lock. The PP would be a subset of the ITT data set, composed of all randomized patients who have no major protocol deviations throughout their entire study period. This PP data set would be used for the secondary supportive analysis of the primary efficacy criterion and serve as a check of its robustness.

Parametric data will be analyzed with ANOVA and nonparametric data with the two-tailed Fisher’s exact test if incidence <5 or the Chi-square test with incidence >5. The inference for the noninferiority will be based on the upper confidence bound. A fully specified Statistical Analysis Plan will be made public before unmasking results. Additional analyses are not planned.

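### As written, the protocol article offers only unadjusted tests for postoperative nausea and vomiting, although the Apfel score is known for every patient before randomization and decides prophylaxis

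*Protocol article*

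**What the plan says.** The Other secondary objectives section includes "the frequency and quantity of postoperative nausea, vomiting and pain". The Participant timeline defines the measures in the recovery unit (PACU): nausea on a 0 to 10 verbal rating scale at admission, every 15 minutes and at discharge, and a count of vomiting.

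The same section lists the Apfel score among the baseline characteristics taken at time point A. Randomization follows at time point B, shortly before surgery. Under General interventions for all patients, the two-drug nausea prophylaxis is given "if the Apfel-Score is ≥2", by the same rule in all three arms.

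On analysis, the Statistical methods section states "Parametric data will be analyzed with ANOVA and nonparametric data with the two-tailed Fisher’s exact test" when the incidence is below 5, and the chi-square test above that. It names no covariate and no stratification factor, and it does not mention nausea or vomiting. It then says "A fully specified Statistical Analysis Plan will be made public before unmasking results" and, directly after, "Additional analyses are not planned".

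**The concern.** The protocol itself treats the Apfel score as a marker of risk for nausea and vomiting, since it allocates prophylaxis by it. Each arm therefore mixes patients who may differ in baseline risk and who certainly differ in prophylaxis. ANOVA, Fisher's exact test and the chi-square test leave that variation in the error term. They also leave uncorrected any difference in Apfel distribution that arises between arms by chance.

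Adjustment would be safe, because the score is fixed before allocation and cannot be affected by the anesthetic. At stake is the precision of one comparison. Neither the validity of the test nor the primary result is in question.

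**Working it through.** **The plan's own figure.** There is none to reproduce. The Sample size section gives no rate, effect or power for nausea or vomiting. The 117 patients per arm (351 in all) come from the cough calculation.

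**Assumed inputs.** The documents give neither the Apfel distribution nor the risk by score, so both are assumed here. Scores 0, 1, 2, 3 and 4 occur in shares w = 0.10, 0.25, 0.30, 0.25 and 0.10. Three gradients of nausea risk r in the PACU are tried.

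**Formulas.** Mean risk p = Σ w·r. Share of variance explained g = Σ w(r − p)² / [p(1 − p)]. Adjustment multiplies the variance of the arm comparison by about (1 − g), so its worth in patients is 351/(1 − g) − 351, and the standard error falls by 1 − √(1 − g).

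| Gradient | r for scores 0 to 4 | p | g | Extra patients | Fall in standard error |
|---|---|---|---|---|---|
| Flat | 0.10, 0.15, 0.15, 0.20, 0.25 | 0.1675 | 0.00157/0.1394 = 0.011 | 4 | 0.6 % |
| Moderate | 0.05, 0.10, 0.20, 0.30, 0.40 | 0.205 | 0.01122/0.1630 = 0.069 | 26 | 3.5 % |
| Steep | 0.05, 0.10, 0.20, 0.40, 0.60 | 0.25 | 0.02825/0.1875 = 0.151 | 62 | 7.8 % |

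**Effect of prophylaxis.** Treating patients with a score of 2 or more lowers risk where it would be highest. Take an assumed untreated gradient of 0.10, 0.20, 0.40, 0.60, 0.80, which gives g = 0.186. If prophylaxis cuts risk by 40 % from score 2 upward, the risks become 0.10, 0.20, 0.24, 0.36, 0.48 and g falls to 0.055. With a 60 % cut they become 0.10, 0.20, 0.16, 0.24, 0.32 and g falls to 0.021. Where the crude test has 80 % power, adjusted power is Φ(2.80/√(1 − g) − 1.96): 87 %, 82 % and 81 % respectively. The gain is then about 1 to 2 points once prophylaxis is allowed for.

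**Collapsed score.** If events are few, the score may have to be reduced to below 2 (share 0.35) versus 2 or more (share 0.65). The mean risks in the two strata are then:
- flat: 0.136 and 0.185, g = 0.004, about 1 patient;
- moderate: 0.086 and 0.269, g = 0.047, about 17 patients;
- steep: 0.086 and 0.338, g = 0.078, just under 30 patients.

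**Chance imbalance.** With 65 % at score 2 or more and 117 per arm, the difference in that share between two arms has standard error √(2 × 0.65 × 0.35/117) = 0.062. A difference of up to 1.96 × 0.062 ≈ 12 points is ordinary chance. Multiplied by the stratum risk differences above, it moves the crude nausea difference by 0.12 × 0.049 = 0.006 (flat), 0.12 × 0.184 = 0.022 (moderate) or 0.12 × 0.253 = 0.030 (steep).

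**The case against.** The strongest reply is that covariates for a low-ranked outcome are normally left to the statistical analysis plan. This article promises such a plan, and it is not at hand. The sentence on tests is a general rule by type of data and fixes no analysis of nausea or vomiting in particular. The line ruling out additional analyses can be read as nothing beyond that plan, so it need not bar a covariate within a listed comparison.

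This narrows the point without removing it. The article is not silent on method: it names a set of tests, all of them unadjusted, and on a plain reading an Apfel-stratified comparison lies outside that set. A reader might go further and infer that the precision has definitely been given away. The documents do not support that, because the unseen plan may add the adjustment.

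It can also be said that an unadjusted comparison of randomized arms is legitimate. That stands in full. The prophylaxis rule is the same in every arm, so randomization balances both score and prophylaxis on average. Finally, the prophylaxis rule weakens the case for adjustment, because it flattens the gradient that adjustment would exploit. That also stands, and it is why the upper end of the range should not be the headline.

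**Conclusion.** The point holds as a minor matter of efficiency. The tests named in the article make no use of a baseline score that every patient has and that the protocol itself ties to this outcome. A reader might infer that mixing patients with and without prophylaxis biases the comparison. It does not, on average; what is lost is some precision and protection against chance imbalance.

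The size cannot be derived from the documents. Under the assumed distribution and gradients it lies between about 4 and 62 patients' worth on 351, with the low to middle part more plausible, and between about 1 and 30 if the score is collapsed to two strata. Nausea and vomiting belong to the other secondary objectives, for which the trial is not sized, so the severity is the lowest.

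**What to change.** Unless it already does so, the promised statistical analysis plan should state before unmasking:

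- Any nausea and any vomiting in the PACU are compared between arms with a Cochran-Mantel-Haenszel test stratified by Apfel score, reported with a stratified risk difference.
- The nausea rating is compared with an ordinal or linear model that includes the Apfel score as a covariate.
- The unadjusted tests are kept as supportive.
- If events are too few for five strata, most likely for vomiting, the score is collapsed to below 2 versus 2 or more, by a rule written down in advance.

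The cost is a few sentences and a few degrees of freedom. No new data are needed and the prophylaxis rule is untouched. Collapsing the strata gives up part of the gain. Fixing the choice beforehand also avoids a later choice between crude and adjusted results.

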### Sample size

Sample-size estimates for both considerations (superiority and noninferiority) were calculated separately. All sample sizes were calculated using a type 1 error, α = 0.05, and power of 0.80. The primary outcome calculations were carried out based on a one-way analysis of variance (same n) with three groups. The variances and means were estimated for the primary outcome variable time to state the date of birth from our meta-analysis [4]. For the sevoflurane, propofol and desflurane groups, means were set to 8.75, 6.8 and 5.6 minutes, respectively. A standard deviation of 3 minutes was considered (these parameters correspond to an effect size (f) of 0.43). A sample size of 19 patients per group is needed to detect such an effect for our superiority hypothesis.

The sample size for the noninferiority hypothesis was calculated based on the secondary outcome variable cough overall (CO). Using the normal approximation to the binomial and assuming a proportion of the outcome in the population between 0.07 and 0.10 and noninferiority bound of 0.20 a sample size of 81 and 112, respectively, is required to claim noninferiority. The margin delta of 20 % was chosen for clinical considerations. We claim that a difference of cough occurrence up to 20 % is clinically not relevant. This is justified by the result of our meta-analysis [4], where the identified coughs had never lead to a serious impact on the patients’ outcomes.

The sample size calculation for noninferiority of treatment is based on a sample size formula published by Blackwelder [7]. Considering data from the literature, a dropout rate of 5 patients per group (for example, requirement of endotracheal intubation, protocol deviations and losses for first postoperative day- follow up) is expected. We decided therefore to include 117 patients per group, to cover the calculated sample size of 19 + 5 patients per group for the superiority hypothesis as well as 112 + 5 patients for the noninferiority hypothesis. Altogether, there will be 351 randomized patients.

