### Randomization

The responsible biostatistician will perform a study-specific computer-generated randomization (study arms, number of blocks and block lengths) according to the study-specific biometric specifications, by using the software framework “R” [8]. The complete randomization list and potential block sizes will only be accessible by the biostatistician of the study. To guarantee adequate allocation concealment, the group assignments will be preserved in sequentially numbered, sealed, opaque envelopes and these will be provided to the principle investigator of each center at the beginning of the study by the biostatistician. The principle investigator will ensure that only the unblinded investigators have access to these envelopes and that they will be opened in sequential order of the patients’ surgery time points. Additionally, he will have to assure that the anesthesia is truly performed according to the assigned intervention, to avoid performance bias. In order to maintain blinding during enrollment and data entry to the electronic case report form (eCRF), two different accounts will be created per center. By utilizing the first user account, access to intraoperative data, as well as randomization, will be possible. Using the second account, entry of pre- and postoperative data will be permitted. Patients in compliance with all inclusion criteria and none of the exclusion criteria will be randomly assigned into one of the three study groups: desflurane, or sevoflurane, or total intravenous anesthesia with propofol.

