Access to randomization is reserved solely to the intraoperative investigator and has to be done shortly before surgery. The time point of envelope opening, the patient initials and the screening number of the patient will be written on the appropriate envelope before it is opened. The envelopes have to be safely stored in the intraoperative patient file. Within a center, the randomization number will occur in succession. The number will contain information about the randomizing study site and the patient sequence. The randomization number will consist of six digits, the first three for the center and the last three for the patient, for example, 001 to 001 (for center 001 and the first patient included). This randomization code will be used to label all information collected for each patient. The monitors of the study will check carefully that the envelopes were really used in the correct sequence and that the signed informed consent occurred definitively before opening of the randomization envelope.

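### Allocation runs within center, but the analyses named carry no center term; adding one is a small and free gain in precision

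*Protocol article*

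**What the plan says.** Protocol article, Randomization: the biostatistician generates a blocked list by computer and keeps any block sizes confidential. Assignments go into "sequentially numbered, sealed, opaque envelopes and these will be provided to the principle investigator of each center". The section adds that "Within a center, the randomization number will occur in succession", and the first three digits of that number identify the center. Study setting names four centers. Stratification by center is never stated in so many words.

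Statistical methods: "Parametric data will be analyzed with ANOVA". Incidences are tested by Fisher's exact or chi-square test according to the count, and noninferiority is judged on the upper confidence bound. No center factor is named. The section promises a full statistical analysis plan, to be public before results are unmasked, and says that no additional analyses are planned.

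Sample size: "The primary outcome calculations were carried out based on a one-way analysis of variance (same n) with three groups".

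General interventions for all patients leaves two aspects of care to the centers. Midazolam premedication follows each center's routine, and the same section says: "Spontaneous breathing or controlled ventilation with LMA will be applied during maintenance of anesthesia, according to the standard operating procedure of each participating center".

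**The concern.** Blocks run out within a center give nearly equal arm numbers there, whether the biostatistician made four lists or cut one blocked list into four runs. Differences between centers then largely cancel from a comparison of arms. An analysis by arm alone still counts those differences as residual noise. Its standard error describes more variability than the arm difference really has, so intervals are too wide and the true error rate falls below the nominal one.

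The protocol gives reasons why centers might differ. Sedative premedication could plausibly shift the time to state the date of birth, and ventilation mode could shift airway reactions. What is at stake is precision, mainly for desflurane against propofol, which is the smaller of the two planned desflurane contrasts.

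**Working it through.** **Inputs from the Sample size section.** "All sample sizes were calculated using a type 1 error, α = 0.05, and power of 0.80". For sevoflurane, propofol and desflurane, "means were set to 8.75, 6.8 and 5.6 minutes, respectively". SD 3 minutes; 19 per group needed for superiority; 117 per group randomized, 112 after the allowed dropout of 5.

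**Assumed.** The share of variance between centers (ICC) is not given; 0 to 0.20 is used. The SD of 3 minutes is taken as the total SD.

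**1. The plan's own figure.** Grand mean = (8.75 + 6.8 + 5.6)/3 = 7.05. Deviations are 1.70, −0.25 and −1.45, with squares summing to 5.055. So f = √(5.055/3)/3 = 0.433, against 0.43 stated. With noncentrality 3·n·f², the one-way F test has power 0.795 at n = 18 and 0.819 at n = 19. The stated 19 reproduces.

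**2. Power at the actual size, without center.** At 112 per group, the F test has power above 0.9999. Pairwise power is 0.847 for desflurane-propofol (6.8 − 5.6 = 1.2 min) and above 0.9999 for desflurane-sevoflurane (8.75 − 5.6 = 3.15 min).

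**3. Interval width.** Without center, the half-width is 1.96 × 3 × √(2/112) = 0.79 min. With center, the residual SD is 3·√(1 − ICC), so the ratio of the two widths is 1/√(1 − ICC).

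| ICC | Half-width without center (min) | Half-width with center (min) | Ratio |
|---|---|---|---|
| 0 | 0.79 | 0.79 | 1.000 |
| 0.05 | 0.79 | 0.77 | 1.026 |
| 0.10 | 0.79 | 0.75 | 1.054 |
| 0.20 | 0.79 | 0.70 | 1.118 |

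**4. Simulation.** 4,000 runs per setting; blocks of 6 within four centers of assumed sizes 150, 90, 60 and 51 (351 in total, no dropout); both models fitted to the same data.

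| ICC | F-test error rate, without / with center | Power for 1.2 min, without / with center | Difference (points) |
|---|---|---|---|
| 0 | 0.050 / 0.051 | 0.861 / 0.862 | 0.1 |
| 0.05 | 0.042 / 0.048 | 0.866 / 0.871 | 0.5 |
| 0.10 | 0.039 / 0.052 | 0.884 / 0.895 | 1.1 |
| 0.20 | 0.032 / 0.053 | 0.894 / 0.924 | 3.0 |

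The simulation error of a rate near 0.05 is √(0.05 × 0.95/4000) = 0.003, so the adjusted rates agree with 0.05. F-test power under the planned means was 1.00 in every cell. Power without center rises with the ICC because the total SD is held at 3, so the loss is relative to the better model, not to the plan's target.

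**5. Cost of the term.** With 351 patients, residual degrees of freedom go from 351 − 3 = 348 to 345. At ICC 0 and 112 per group, calculated pairwise power is 0.847 with or without center.

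No corresponding figure was computed for the cough difference.

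**The case against.** The strongest reply is that the article does not fix an analysis without center. Statistical methods says ANOVA, and a model with arm and center is also an ANOVA. The one-way description belongs to the sample-size calculation, and sizing on a simpler model than the one fitted is routine. The full model is left to an analysis plan that is not shown. All of this stands: a reader might infer that center has been ruled out, but nothing in the article says so. What remains is that every method named lacks a center term, and that Fisher's exact and chi-square tests, as named, have no place for one.

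Balance within center is likewise inferred from center-held envelopes, within-center numbering and blocking. It is the natural reading, but it is not stated.

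A reader might also take it as fact that the intervals are too wide and power is lost. The documents do not support that either. The effect depends on an unknown between-center variance and vanishes at zero. Much of the conduct is common to all centers, including the BIS target and the 20-second command interval. Power for the 1.2-minute contrast stays above 0.80 without center in every case tried.

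Finally, one might want Cochran-Mantel-Haenszel tests for all airway events. That goes too far. Even for cough, at the expected 7 to 10 %, about 117/4 ≈ 29 patients per arm and center would yield only 2 to 3 events. Laryngospasm was rare in the sponsor's meta-analysis, and dropping the exact test there has no demonstrated benefit.

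**Conclusion.** The point holds as a minor, free improvement. Allocation appears to be balanced by center, and the analyses named do not use center. To the extent that centers differ, intervals for emergence times are about 3 to 12 % wider than needed at an assumed between-center share of 5 to 20 %, and not wider at a share of zero. Power forgone on the desflurane-propofol contrast is about 0 to 3 points; the overall F test loses none. The error is in the conservative direction, so a positive superiority result is not put in doubt.

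These sizes rest on the assumed shares, a total SD of 3 minutes, blocks completed within center, and assumed center sizes and block length. The direction is standard; whether the final model already contains center cannot be told from the article.

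**What to change.** State in Statistical methods, or confirm in the analysis plan before unmasking, that:

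- emergence times are analyzed by a linear model with arm and center (four levels) as fixed effects, with desflurane versus sevoflurane and desflurane versus propofol taken as contrasts from it;
- the cough risk difference and its upper noninferiority bound are stratified by center with Mantel-Haenszel weights;
- Fisher's exact test is kept for rare events such as laryngospasm.

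The cost is a few sentences and three residual degrees of freedom. Center is already coded in the randomization number, so no new data are needed. If the analysis plan already does this, one confirming sentence closes the point.
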